### Study methods and procedures

All children admitted at the three centres with an acute history of gastroenteritis will be screened for study inclusion by the paediatric triage/admission team. All eligible children will be admitted to designated areas (so children can be closely monitored) in Mbale, Soroti, and Kilifi hospitals’ acute paediatric wards and if parents/guardian give consent to participate, children will be randomised to their treatment allocation by study clinicians (nurses or doctors) using cards in opaque sealed envelopes. The clinical procedures and laboratory investigations for both those in stratum A and B are summarised in
Table 1
^
23
^.

**Table 1. T1:** Schedule of clinical assessments and laboratory investigations
^
23
^.

Hours (h) /Days (d)	0*h	8h	24h	96h	7d	28d
Consent and information sheet	X					
Clinical examination (doctor/doctor visit)	X	X	X		X	X
Nurse observation/visit		X	X		X	(X)
Vital observations, anthropometry	X	X	X		X	X
Survival Status				X	X	X
Laboratory investigations						
Haematology	X		X		(X)	(X)
Biochemistry (Chemistry and Osmolarity)	X	X	(X)		(X)	
Lactate/Glucose	X	X	(X)			
Malaria slide + /- RDT	X		(X)		(X)	(X)
Blood culture ^$^	X					
HIV testing	X					
Urine (dipstick and save)	X	(X)	(X)		(X)	
Cross match (for transfusion) (red top) if indicated	X					
Stored samples						
Plasma for Cardiac Biomarkers ^$^	X	X	X		X	
Urine for osmolarity ^$^	X	X	X		X	

*at enrolment (X) optional 
^^^ Day 7 and Day 28 if child is discharge and NOT able to return then confirmation of survivorship can be done by telephone
^S^ optional

### Consent process

Once eligibility has been confirmed, authorized trial staff will approach parents/guardians to invite their child to take part in the trial. An information sheet will be provided to the parent/guardian in their usual language containing details of the GASTROSAM trial. The sheet will be read aloud to those who are unable to read. The doctor/nurse will check that the information has been fully understood and parents/guardians will be encouraged to ask questions they may have about their child’s participation in GASTROSAM. The information sheet and consent include details of the clinical trial, follow up, and additional biological samples taken for the trial and permissions for sample storage. Where possible, prospective written informed consent will be sought from parents/guardians who will then be asked to sign the consent form
^
24
^. Consent will include permission for the collection of admission and follow-up blood samples for later aetiological investigations. If parents/guardians are unable to sign, a thumbprint will be taken in lieu of a signature. A copy of the consent form will be given to the parent/guardian, the original placed in the patient’s medical notes, and a copy kept in the investigator site file.

A number of children will present as emergencies where delay in study enrolment, and thus treatment, will not be practical or indeed humane. We will use a modified form of deferred consent, developed for the FEAST (Fluid Expansion As a Supportive Therapy) trial
^
25
^ which we have now received ethical approvals for
26). This involves a ‘two-stage’ consent process where verbal assent is initially sought from parents or guardians by the admitting medical team, if it is considered that the full consent process would significantly delay treatment allocation, and consequently could be detrimental to the child’s health. Full consent is obtained once the child’s clinical condition has been stabilized. Caregivers will be provided with a brief verbal description of the trial and will be given the opportunity to ‘opt out’ of clinical. As in the FEAST trial, if following an assent process a child died prior to full written consent, full consent would not be sought.

### Treatment allocation

Following consent, children will be randomly allocated to the treatment arms. Children in Stratum A with severe dehydration will be simultaneously assigned two randomisations (one for the intravenous rehydration strategy in a 1:1:2 ratio) and one for the oral rehydration strategy (1:1 ratio)). Children in Stratum B will be randomised to oral rehydration strategies (1:1 ratio). See Trial flow
Figure 1. Randomisation lists will be generated stratified by site and stratum using permuted blocks of variable sizes and kept at the Medical Research Council (MRC) Clinical Trials Unit at University College London, London. Opaque sealed envelopes containing the randomised allocation will be prepared before the trial at the Clinical trials facility, KEMRI Wellcome Trust Research Programme (KWTRP), Kilifi. These will contain the actual allocation visible only once opened. The cards will be numbered consecutively within each stratum and opened in numerical order. Clinicians will be aware of the treatment-group assignments, but the laboratory tests are to be performed in a blinded manner.

**Figure 1. f1:**
[figure not shown]
Trial flow.

### GASTROSAM Stratum A (Intravenous rehydration and ORS)

Signs of severe dehydration treatment Arms 1:1:2

i) WHO Plan C arm: Rapid intravenous rehydration as per WHO Plan C (usually for non-SAM children) (100mls/kg Ringers Lactate (RL) over three – six hours according to age including boluses (20mls/kg) for those with shock)ii) Slow Rehydration Arm: A slower intravenous rehydration regimen (100 mls/kg RL started immediately and given over eight hours (and no additional boluses for shock). iii) WHO SAM arm: rehydration regime: ORS and intravenous boluses of RL only for shock (standard of care) 

A second (simultaneous) randomisation for children in this stratum (for all three iv rehydration strategies) will be to one of two oral rehydration solutions received by children in Stratum B (see below).

Children presenting with some (moderate) dehydration (defined as two of restlessness or irritable; thirsty, sunken eyes or skin pinch goes back slow (<=two seconds) and thus not in Stratum A will be randomised to one of two oral rehydration solutions (GASTROSAM Stratum B) (ratio 1:1 for both groups). 

### GASTROSAM Stratum B (ORS only)

i) Standard WHO ORS given for non-SAM (experimental) versus ii) WHO SAM-recommended low-sodium RESOMAL

Both oral rehydration solutions will be given in accordance with WHO Plan B oral rehydration regime over four hours. Treatment will be given according to requirements during hospitalisation (and may include continuing or restarting ORS to replace on-going losses or intravenous rehydration if there’s development of severe dehydration). All children can start ORS as soon as they are able to take and retain oral fluids, even before intravenous rehydration is complete (which is replacing deficit). For children unable to take fluids orally we will consider temporary placement of nasogastric tubes. 

### Clinical management and monitoring

Following correction of severe dehydration (based on a review of WHO clinical signs and observations), children will be assessed for their ability to take oral rehydration or feeds. Children who are able to take and retain oral fluids/feeds and who are in neutral or marginally positive fluid balance (both input and output will be measured) will be considered as satisfactorily rehydrated.

All children will be offered oral rehydration fluids alongside their intravenous rehydration regimen; in GASTROSAM this will follow the randomised treatment allocation. Each child will have an input-output monitoring chart, i.e., including urinary catheter volumes and diaper weights, to document the volumes that children in both arms are drinking and retaining as well as defining clinical endpoints that will be used to guide when to stop intravenous fluids in future studies. For the purposes of this study, each child will aim to complete their allocated intravenous fluid hydration regimen.

### Management of potential complications

Children enrolled in GASTROSAM will be very closely monitored, using the same systems for adverse event reporting used in the fluid resuscitation, FEAST trial
^
25
^, and the transfusion TRACT trial
^
27
^ that examined more liberal volumes of fluid and blood respectively than was currently recommended enrolling at the centres involved in the current GASTROSAM trial. Prior to the start, the study teams will undergo detailed training and clear guidelines on what signs to look for and how to treat suspected fluid overload or heart failure will be included in the manual of operations, which are similar that which were developed and implemented in the FEAST trial
^
25
^. Irrespective of which arm of the trial patients are included in, the treatment of life-threatening side effects would be assured. This would include prospective monitoring for pulmonary oedema or signs of cardiac failure or the development of severe hypotension which would be treated with a fluid bolus therapy to restore systolic blood pressure. Mechanical ventilation is not available any of the hospitals which largely reflects the typical situation in most hospitals in sub-Saharan Africa. In the case of a child who develops clinical signs and fluid overload, the management plan is to stop intravenous fluids and, if there are clear signs of pulmonary oedema/heart failure, to administer intravenous frusemide and oxygen, monitoring the child closely with hourly observations until stable and further fluid management to be administered orally (or via nasogastric tube if the child is unable to take fluids orally). 

If, after the initial rehydration regimen is completed, there are ongoing significant gastrointestinal fluid losses, this will be managed according to clinical signs which, if severe dehydration or shock develops may include one repeat of intravenous regime previously allocated protocol and then, personalised fluid management to take account of input/output.

## Clinical endpoints

### Primary outcome

For intravenous rehydration: Mortality at 96 hours.

For oral rehydration strategy: change from randomisation (=0 hours timepoint) in sodium levels at 24 hours. 

### Secondary outcomes

Measures assessing safety (evidence of pulmonary oedema or heart failure); change in plasma sodium levels from baseline (time of enrolment(=0 hours timepoint)) to completion of intravenous rehydration levels (8 hours) for those in Stratum A; perturbations of electrolyte abnormalities (severe hyponatraemia <125 mmols/L or hypokalaemia <2.5 mol/L) over 8 hours, weight and MUAC change to 96-hours and Day seven; and Day-28 survival.

If possible children should be catheterized (not mandatory) in order to achieve accurate fluid balance calculations. The urinary catheter can be removed after eight hours. All children will have a daily weight and fluid balance calculated until discharge (performed at the same time each day) and at follow up. All children will be followed up on Day seven and Day 28 (post enrollment) to confirm survivorship status. Where children are able to attend for clinical follow up they will be reviewed by a clinician, have their weight and observations recorded. All children will also have one further blood sample, where laboratory facilities permit. (for biochemistry and cardiac enzymes) taken on Day seven. Follow up clinical assessments of hydration (in children without any on-going losses or intercurrent illness) serve to validate inpatient assessments of hydrations status. Prior to the day of follow up the parents will be contacted by the study site coordinators to remind them of the clinic visit. This system has previously been used in the FEAST and TRACT trial and lead to very high study retention and follow-up
^
25,
27
^.

Clinical and haemodynamic (vital signs) responses will be monitored every 30 minutes for the first two hours then hourly until eight hours, and every 4–8 hourly up to 24 hours and then every 12 hours until discharge, as will pre-specified serious adverse events (SAEs) of interest:

a) new onset seizures or worsening conscious level

b) signs of pulmonary oedema

c) and/or cardiac failure after the initiation of intravenous rehydration

Time to tolerate oral fluids/feeds and maintenance of normal fluid balance and time to discharge will also be collected

### Adverse events and interim analyses

SAEs will be reviewed immediately by a designated physician (SAE reviewer) and reported to the appropriate ethics and regulatory committees within one week. Severe adverse events will use the standardized definitions and external review process of these events will be carried out using the same criteria as were used in the FEAST trial. All relevant adverse events are reported in the case report form (CRF) and SAE form. The reporting procedure is captured within the safety reporting SOP. Any questions concerning adverse event reporting should be directed to the study coordination centre in the first instance (Kilifi). The Chief investigator will inform the Trial Steering Committee (TSC) and Data Monitoring Committee (DMC) for review on a regular basis (as deemed necessary).

### Auditing

The study will be monitored by the Trial Management Team from the Kilifi Clinical Trial Facility (KEMRI-Wellcome Trust). The monitors have been trained on the study protocol and will be familiar with all study procedures. During the initial visits, the monitors will review 100% of the fields of all the study forms. Subsequently the monitors will review 100% data contributing to the primary endpoint and 100% of fields for a randomly selected sample of study forms. All forms monitored during a visit will be detailed in the monitoring visit report. A database check for accuracy of data entry is performed at regular intervals. The data points are to be checked will be endpoint data and safety data. After site initiation visit (SIV) the first routine visit will be done after the first five participants are enrolled then the other routine visits depending on the rate of recruitment and issues raised during the initial visit the frequency of the routine visits will be decided thereafter. The SIV was done on 20
^th^ August 2019 for the Mbale site and 28
^th^ August for the Soroti site. The 1
^st^ routine monitoring on site visits were done on 4
^th^ and 5
^th^ Feb 2020 respectively. The SIV and enrollment started in Kilifi County Hospital on 13
^th^ June 2021, and at Coast General Hospital, Mombasa on 17
^th^ June 2022. The SIV for the MSF are anticipated in the last quarter of 2023.

### Data management

All clinical and laboratory data will be recorded in the case report form and stored with a unique serial number identifier. Data will be entered (double data entry) onto the Open Clinical database. All data will be regularly backed up and backup copies stored both on and off site. Paper records will be archived in locked cabinets at the respective study sites. These cabinets will have limited access with prior authorisation (by the site principal investigators). All data will be partially- anonymized prior to presentation or publication of any results. Study participants will be identified by a unique subject identification number, but patient identifiable information will not be recorded on the study database in compliance with good clinical practice (GCP) requirements. The data will be examined for inconsistencies during the trial by the statistician and fed back to study sites for corrections following GCP procedures.

### Confidentiality

All clinical data will be held confidentially, and personal identifiers will be removed before analysis of the data and presentation of the results.

### Data sharing

After completion of the study, requests for data access from researchers outside the study team will be considered by the trial management team and clinical trials unit (Data Governance Committee), and where indicated, requestors will be asked to develop scientific protocols for approval of secondary analyses. The potential to share data will be included in the participant Information and Consent Form
^
24
^.

## Ethics statement

Ethical approvals have been obtained from Mbale Regional Hospital Research Ethics committee (MRRH_REC OUT 107/2018) for both Mbale and Soroti Regional Referral Hospital sites, from KEMRI Scientific and Ethics Review Unit (SERU) for the Kilifi County Hospital site (KEMRI/RES/7/3/1) and Coast General Teaching and Referral Hospital, Mombasa; from Médecins Sans Frontières Ethical Review Board (MSFERB 2293) from
*Comité National d'Ethique pour la Recherche en Santé* (CNERS), reference 47/2023/CNERS and National Health Research Ethics Committee from Nigeria (NHREC Approval Number NHREC/01/01/2007-04/10/2023). The trial has been registered on ISRCTN (registry identifier 76149273) on 8
^th^ August 2018 (Version 1.0), updated on 7
^th^ August 2023 (Version 3.0) and the Pan African Clinical Trial Registry (
www.pactr.org) database (identifier PACTR202103852542919) on 23
^rd^ March 2021 (Version 2.0), updated on 7
^th^ August 2023 (Version 3.0).

### Safety

The study will be performed in patients who may potentially benefit from the treatment. The risks of cannula insertion and blood drawing include pain, infection at the site of the cannula, and thrombophlebitis. These will be minimised by careful technique according to a standard SOP, cannula site inspection, and replacement or removal where necessary. No more than 1ml/kg of blood will be drawn for research at any one time
^
10
^.

Whilst there is a concern that liberal fluid rehydration may cause heart failure, our recent publication on myocardial function in this population given rehydration did not show this resulted in heart failure
^
16
^. Children enrolled in GASTROSAM will be very closely monitored, using the same systems for adverse event reporting used in the FEAST trial
^
25
^ and the transfusion (TRACT) trial
^
28
^ both examined more liberal volumes of fluid and blood respectively than was currently recommended. Blinded SAEs (removing all references to intervention arm) will be independently adjudicated by an endpoint review committee.

In neither the FEAST nor the TRACT trial were any concerns raised by the data monitoring committee that more liberal volumes were causing fluid overload. GASTROSAM will be conducted in three of the trial sites for FEAST and TRACT and are familiar with the conduct of trials in critically sick children. All study teams will undergo detailed training and included in the manual of operations will be clear guidelines on what signs to look for and how to treat suspected fluid overload or heart failure, which were developed and implemented in the FEAST trial.

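### Cardiac failure as an SAE of interest is tied to the start of intravenous rehydration, so the described blinding of adjudicators may be incomplete and the event is not defined alike in all arms

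*Protocol article*

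**What the plan says.** The trial is open-label. Under Treatment allocation: "Clinicians will be aware of the treatment-group assignments". The safeguard for serious adverse events appears in the Ethics statement, under Safety: "Blinded SAEs (removing all references to intervention arm) will be independently adjudicated by an endpoint review committee".

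The Secondary outcomes section uses the fluid-overload events in two ways. The secondary outcome is "Measures assessing safety (evidence of pulmonary oedema or heart failure"), with no condition on treatment received. The list of pre-specified SAEs of interest then separates item (b), "b) signs of pulmonary oedema", from item (c), "and/or cardiac failure after the initiation of intravenous rehydration".

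For fluid overload, Management of potential complications says "the management plan is to stop intravenous fluids and, if there are clear signs of pulmonary oedema/heart failure, to administer intravenous frusemide and oxygen". In Stratum A, both liberal arms receive 100 mL/kg of Ringer's lactate intravenously, over different periods. The WHO SAM arm receives "ORS and intravenous boluses of RL only for shock (standard of care"). The Statistical analysis section compares pulmonary oedema and heart failure by time-to-event methods to day 28. It does not say whether adjudicated or reported events enter that comparison.

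**The concern.** Removing references to the arm works well when treatment leaves little trace in a case narrative. Here, whether intravenous rehydration started, and when, is close to the Stratum A allocation itself, and item (c) builds that fact into the event. An adjudicator applying item (c) literally must be told something that points towards the arm. The same wording makes the event unequal between arms, because a control child who stays on oral fluid throughout cannot qualify, whatever the clinical picture.

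Pulmonary oedema and heart failure are the harms that the current guideline fears from liberal fluid, and the article's Discussion makes guideline revision depend on safety as well as mortality. If adjudicators can partly infer the arm, they might confirm overload more readily, or less readily, in children who had an infusion. The comparison could shift in either direction while being described as blinded.

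**Working it through.** There is no figure in the plan to reproduce; the point rests on setting the sections side by side.

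1. **Blinding rule (Safety).** References to the intervention arm are removed. On a narrow reading only labels go, and fluid details stay in the file. On a broad reading the fluid details go too.
2. **Event definition (Secondary outcomes, item (c)).** Cardiac failure counts only after intravenous rehydration has begun. On the narrow reading of step 1, the file carries arm information. On the broad reading, the committee alone cannot check the timing condition; someone else must.
3. **Who can meet item (c).** Every child treated as allocated in the two liberal arms can. A WHO SAM child can do so only if given intravenous fluid.
4. **What is not tied to intravenous fluid.** Item (b) stands on its own line without the condition, and so does the secondary safety outcome. The opening and/or of item (c) could be read as extending the condition to item (b), but the text does not require that.
5. **Source of the reports.** Treating clinicians know the allocation. The management plan for overload refers to stopping intravenous fluids, so an unmasked narrative of an event managed to plan would probably record it.

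**How informative is visible intravenous fluid?** Inputs:
- Allocation in Stratum A is 1:1:2 (Treatment allocation), so the prior probability of a liberal arm is (1+1)/4 = 0.5.
- All children in the liberal arms receive intravenous fluid by design.
- s is the share of WHO SAM reports that show intravenous fluid. The documents do not give it, so it is an assumption shown over a range.
- Reports are assumed equally frequent in the liberal and control groups.

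By Bayes' rule, P(liberal arm | intravenous fluid shown) = 0.5 / (0.5 + 0.5s) = 1/(1+s).

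| assumed s | P(liberal arm) |
|---|---|
| 0.10 | 1/1.10 = 0.91 |
| 0.25 | 1/1.25 = 0.80 |
| 0.50 | 1/1.50 = 0.67 |
| 0.75 | 1/1.75 = 0.57 |
| 1.00 | 1/2.00 = 0.50 |

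A report showing that no intravenous fluid was given points to the WHO SAM arm. Visible exposure is therefore a cue unless nearly all control reports also show intravenous fluid, but it does not identify the arm. Exposure alone also does not separate Plan C from slow rehydration.

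**The case against.** The strongest reply is that the phrase about references to the arm can be read to cover fluid details, and that nothing shown says those details stay in the adjudication file. Adverse events and interim analyses refers to a safety reporting SOP and to review criteria taken from an earlier fluid trial. Masking detail would commonly sit in such a document or in a committee charter, and its absence from a journal article is not a fault. This stands. A reader might infer that the fluid-overload outcome is not adjudicated blind; the documents do not support that.

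A second reply is that the rule and item (c) can coexist. The designated SAE reviewer sees each SAE and could check the timing condition, leaving the committee to decide only whether cardiac failure occurred. This also stands, so it would be too strong to say that the two sentences cannot both be followed. The article does not describe such a division of work, however, and it would not cure the unequal definition in item (c).

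Third, intravenous fluid is not the same as arm. Control children in shock receive boluses. GASTROSAM Stratum B allows intravenous rehydration if severe dehydration develops, and Management of potential complications provides a bolus for severe hypotension in any arm. It would be wrong to say that exposure separates liberal from control in every child without shock.

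Fourth, only item (c) is clearly conditioned, and the analysis section does not say that it uses adjudicated events. That narrows the point but does not remove it.

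Finally, clinicians who know the arm may under-report in any open-label trial. Observations follow one schedule in all arms and monitoring covers safety data, so this is a secondary matter.

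**Conclusion.** The point holds in limited form. Two things follow from the text itself: item (c) as worded calls for information correlated with arm, and a WHO SAM child never given intravenous fluid cannot meet it. That the blinding is incomplete in practice is a possibility that depends on masking rules not shown.

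The size of any bias cannot be derived from the documents. A reader might attach a number to it. With 135 children per group, 10% suspected overload in each (13.5 reports) and no true difference, confirming 65% of liberal-arm reports and 45% of control reports gives 8.8 v 6.1 events, a risk ratio of 0.65/0.45 = 1.44; reversing the rates gives 0.69. The arithmetic is right, but the 10%, 65% and 45% have no source, and applying them by group assumes that no control report shows intravenous fluid. It shows only that the direction is open.

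Adjudication does not affect the 96-hour mortality endpoint. The change is still worth making, because the affected comparison is the main safety question about liberal fluid and the remedy is cheap.

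**What to change.** 1. In Secondary outcomes, define item (c) identically in all arms, as cardiac failure after randomisation.
2. In Safety, state that adjudication has two steps. First, the committee classifies pulmonary oedema, cardiac failure and neurological events from signs and vital observations timed from randomisation. Masked at this step are fluid type, route, volume, rate, start and stop times, input-output charts, serial weights, and statements such as that intravenous fluids were stopped. Weights belong on this list because 100 mL/kg is about 10% of body weight and could reveal the regimen. That classification is locked. Only then are fluid data released, to judge relatedness.
3. In Statistical analysis, state that the comparison of pulmonary oedema and heart failure uses the locked classification.
4. Optionally, send to the same committee any Stratum A child whose charted observations meet the overload signs in the manual of operations, or who received frusemide, even if no SAE was filed.

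If a charter or SOP already contains the masking rule in step 2, citing it is enough for that step; step 1 is still needed.

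The cost is a wording change in the protocol and committee charter, preparation of masked packets, and a second adjudication step. Enrolment began in September 2019, so SAEs adjudicated before the change would need re-review or separate reporting. No additional patients or procedures are required, and no treatment rule changes.
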